**3. STUDY DESIGN**

**3.1 Intervention study**

This study is a double-blind cross-over intervention (challenge) study, planned to run (incl. a 2 week break during Christmas/ new year) from 20-10-2008 till 15-02-2009. A total of 20 healthy male individuals will receive a) a milkshake containing 95g of fat (high-fat challenge) or b) a milkshake containing the same nutritional and energetic value of an average breakfast (based on ‘voedselconsumentenpeiling’ 2003 from TNO). Data obtained with this ‘control’ milkshake will not directly be compared to the HF milkshake, but will be used to obtain knowledge about normal circadian rhythms in EF. Both interventions will be performed in triplicates, to obtain information on variation in the different measures of EF and the variation in PBMC gene expression, white blood cell activation markers, plasma cytokine profiles and other plasma markers of ED. This means that each individual will visit the department on 6 different days. All testing days will be randomly divided over the study time period, with a minimal period between the testing days of 7 days, in order to exclude carry over effects. Randomization is performed in which only the variants ABABAB and BABABA are possible. Two participants will be evaluated on each testing day (see paragraph 6.2.4)

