***6.1.2 Measurements of secondary study outcomes***

Blood samples will be taken from the left arm, which is opposite to the one used for measuring functional ED measures at baseline (-1.5h) and at 1, 2, 3, 5, 6 hours after the milkshake by using a venflon.

**PBMC gene expression profiles** will be determined by using whole genome NuGO Affymetrix microarrays at baseline (-1.5h) and 3 and 6 hours after receiving the challenge. Expression profiles of genes selected from the microarrays will be assessed at all other blood collection time points by quantitative real time PCR (Q-PCR)

**White blood cell activation markers** will be determined at baseline and after 3 and 6 hours by using flow cytometry analysis (coulter Epics XL.MCL flow cytometry by Beckman Coulter)

**Plasma cytokine profiles** will be tested by quantitative immunoassays at rules Based Medicine laboratories (Austin, TX) at all blood collection time points. The cytokine profile of a panel of 120 proteins including will be determined. For detail on the 120 proteins, see:

<http://www.rulesbasedmedicine.com/services_human_antigen.asp>.

**Known plasma markers of endothelial function such as** NO, NOx, prostacyclin, cyclic adenosine monophosphate, cyclic guanosine monophosphate, cytokines, endothelin, intercellular adhesion molecule-1, vascular cell adhesion molecule-1, von Willebrand factor, plasminogen activator inhibitor-1, or thrombomodulin, selectins, integrins, HDL functionality, HDL lipid mediators and extracellular phospholipase secretory phospholipase A2-IIA will be determined at baseline and after 3 and 6 hours. Markers that are changed at these time points will also be measured at all other blood collection time points by using quantitative immunoassays, ELISA and at rules Based Medicine laboratories (see above).

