**6.2.4 Intervention**

Participants will be asked to check in 30 min prior to the first data collection point (T=-2h) in order to be sure that measurements are taken at a ‘resting’ state. Before the start of each study day, the Hb value of each participant will be determined by using a hemoglobin analyzer (HemoCue 201). Participants with a Hb value below 8.4 mmol/L will not be measured and are asked to make a new appointment. If Hb values are normal (e.g. above 8.4mmol/L), a venflon will be placed into the antecubital vein of the participant’s forearm by qualified and experienced personnel. Functional measurements will be performed at baseline (T= -1.5h) and 3 and 6 hours after the intervention. The total time required for the functional measurements is set at 1.5 hours in total and the protocol is as followed:

- 15 min prior to the measurements, participants are asked to lie down on the bed
- Blood pressure will be measured (required for some measures below)
- Macro vascular regional arterial stiffness will be assessed by tonometry
- Macro vascular local carotid arterial stiffness will be assessed by ultrasound
- Macro vascular blood circulation will be assessed by FMD/ ultrasound
- Micro vascular blood circulation will be assessed by iontophoresis

Blood will be collected at baseline (T=-1.5) and 1, 2, 3, 5, and 6 hours after the intervention. An overview of the data collection points on each study day is shown in table 2.

**Table 2:** *protocol on each study day. NB. Data will be collected for two participants each day. The second participant will receive the same protocol, only all time points are delayed by one and a half hour.*

| Intervention time, after overnight fasting (in hours (h)) | -1.5h | 0h | 1h | 2h | 3h | 5h | 6h |
| --- | --- | --- | --- | --- | --- | --- | --- |
|  | (7.30am) | (9.00am) | (10.00am) | (11.00am) | (12.00am) | (14.00am) | (15.00am) |
| Consumption of the test meal |  | X |  |  |  |  |  |
| **Primary measurements** |  |  |  |  |  |  |  |
| Macro vascular:  Arterial stiffness  by tonometry | X |  |  |  | X |  | X |
| by ultrasound | X |  |  |  | X |  | X |
| Flow mediated dilatation | X |  |  |  | X |  | X |
| Micro vascular:  Iothophoresis | X |  |  |  | X |  | X |
| **Secondary measurements** |  |  |  |  |  |  |  |
| Total blood sampling (ml) | 56 |  | 8 | 8 | 56 | 8 | 56 |
| PBMC gene expression |  |  |  |  |  |  |  |
| By microarray analysis | X |  |  |  | X |  | X |
| By Q-PCR | X |  | X | X | X | X | X |

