**8. STATISTICAL ANALYSIS**

To observe an effect of HF on EF, changes in primary outcome variables will be tested using repeated measures ANOVA (mixed model) using pre-defined contrasts, i.e. 3 versus 0 hrs and 6 versus 3 hrs. ANOVA will also be used to quantify the within- and between subject variation of the various measurements.

Changes in secondary outcome variables will be tested using repeated measures ANOVA (mixed model) using pre-defined contrasts, i.e. 3 versus 0 hrs and 6 versus 3 hrs. Additionally, incremental areas under the curve will be calculated for all significant altered secondary outcome variables using the trapezoïdal rule and compared between meals using one-way ANOVA. All statistical analysis will be performed with SPSS version 15.0.

Data analysis of the microarrays will be performed using a Bayesian linear regression model (implemented in the software package LIMMA; [www.bioconductor.org](http://www.bioconductor.org/)). Raw microarray data will be normalized using RMA quantile normalization. Statistically significant changed genes will be identified by student paired t-test followed by a false discovery rate correction (FDR) The latter is used to correct for multiple testing.

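### Secondary-marker AUCs are compared between meals by baseline subtraction without covariate adjustment, which gives up some precision that the pre-meal samples could recover at almost no cost

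*Protocol*

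**What the plan says.** Section 8 tests secondary markers over time (3 versus 0 h, 6 versus 3 h) in a repeated-measures mixed model. It then adds, for markers found to have changed, that "incremental areas under the curve will be calculated for all significant altered secondary outcome variables using the trapezoïdal rule and compared between meals using one-way" analysis of variance. This is the only explicit between-meal test in the section. Meal is its one factor, and no baseline covariate or participant term is named.

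Section 6.1.2 has blood drawn "at baseline (-1.5h) and at 1, 2, 3, 5, 6 hours after the milkshake by using a venflon", so each curve has one pre-meal value and up to five later ones. White-cell activation markers have fewer: they "will be determined at baseline and after 3 and 6 hours by using flow cytometry analysis". Section 3.1 adds that "Both interventions will be performed in triplicates", so each man contributes three curves per meal, each with its own single baseline.

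Section 3.1 also says that the control-shake data are there to describe circadian variation and are not meant for direct comparison with the high-fat shake. That does not sit with the between-meal test in Section 8.

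**The concern.** Subtracting the baseline is the same as regressing on it with the slope forced to 1. If the best slope differs from 1, day-to-day and assay noise in that one fasting sample is carried into the iAUC more heavily than it should be. The post-meal part is averaged over as many as five samples; the subtracted part is not averaged within the day. The baseline is a valid covariate, since it precedes each test meal, and it is already being collected.

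What is at stake is the precision of the between-meal contrast for markers that reach this step. Repairing the error term alone would not help, because a correct within-subject model for the iAUC carries the same baseline noise.

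**Working it through.** **Plan's own figure.** The 20 subjects in Section 4.4 reproduce: a paired t-test with difference 3, SD 4.5 (read as the SD of the paired difference) and two-sided 5% has 80.7% power at n = 20. That figure is for iontophoresis. No power is stated for any marker or for the iAUC test, so 80% below is only an anchor.

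**Inputs from the protocol.** Samples at -1.5, 1, 2, 3, 5 and 6 h; 20 men; 3 days per meal.

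**Assumptions.** Within-man, within-day correlation rho between samples, the same for all pairs; post-meal SD equal to k times the baseline SD. Neither is in the protocol.

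**Weights.** With the baseline placed at 0 h, the trapezoid weights on the increments are 1, 1, 1.5, 1.5 and 0.5 h, sum 5.5 h. So iAUC = 5.5 × (P − B), where P is the weighted post-meal mean and B the baseline. The coefficient of B relative to P is exactly −1. Expressed per hour of the 6 h curve it is 5.5/6 = 0.92, which is the same quantity. The sum of squared normalised weights is 6.75/30.25 = 0.223.

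**Variances (baseline variance 1).**
- Var(P) = k² × [rho + (1 − rho) × 0.223]
- iAUC: Var(P) + 1 − 2 × k × rho
- Adjusted: Var(P) − k² × rho²
- Difference: (1 − k × rho)², which is never negative and is zero when k × rho = 1

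Averaging over three days divides both variances by 3 and leaves their ratio unchanged.

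**Equal variances (k = 1), paired analysis, six samples.** Power is from simulation with the slope estimated (18 against 19 degrees of freedom), iAUC anchored at 80%.

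| rho | iAUC variance | adjusted variance | ratio | power after adjustment |
|---|---|---|---|---|
| 0.3 | 0.856 | 0.366 | 0.43 | 98% |
| 0.5 | 0.612 | 0.362 | 0.59 | 94% |
| 0.7 | 0.367 | 0.277 | 0.755 | 88% |
| 0.8 | 0.245 | 0.205 | 0.84 | 84% |
| 0.9 | 0.122 | 0.112 | 0.92 | 81% |

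For markers with only -1.5, 3 and 6 h the powers are about 95%, 91%, 86%, 83% and 80%. Starting the trapezoid at -1.5 h moves the six-sample powers by less than 1 point.

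**Unequal variances.** Using power = Φ(2.802/√ratio − 1.960), six samples, rho 0.5:
- k = 1: ratio 0.59, 95% (94% in the simulation)
- k = 1.25: ratio 0.80, 88%
- k = 1.5: ratio 0.93, 83%
- k = 2: ratio 1.00, 80%

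At rho 0.8 and k = 1.25, k × rho = 1 and the gain is also nil. It is not nil everywhere above k = 1: rho 0.3 with k = 1.5 gives 91%, and rho 0.8 with k = 2 gives 92%.

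**Men differing in meal response.** With k = 1, rho 0.5 and man-by-meal variance half the within-man variance, the ratio is (0.362/3 + 0.5)/(0.612/3 + 0.5) = 0.88, and power is about 85%.

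**Planned one-way layout, adding only the covariate.** Set between-subject variance equal to within-subject variance, k = 1. At rho 0.5 the iAUC variance is still 0.612, and the adjusted variance is 1.612 − 1.5²/2 = 0.487. The ratio of iAUC to adjusted variance is 1.26, power 88%. At rho 0.7 and 0.9 the ratios are 1.14 and 1.04, power 85% and 82%.

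**The case against.** The strongest reply is that this is a low-stakes analysis. It is supplementary, applies only to markers already changed over time, and may not be intended at all given Section 3.1. The time contrasts, which address whether a marker changes after the high-fat meal, are untouched. That stands, and it sets the severity.

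A second reply is that covariate choice is usually left to the SAP. This carries less weight, because the protocol names a summary and a test that together exclude adjustment.

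A third is that the gain is uncertain. This also stands: rho, the SD ratio and the man-by-meal variance are all missing from the protocol.

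A reader might infer several stronger things that the document does not support:
- **That the meal effect is biased.** It is not: the baseline precedes each meal in a randomised cross-over. Regression to the mean here is another name for the noise already counted.
- **That subtraction is worse than ignoring the baseline.** Under the planned one-way layout it usually helps, because it removes differences in men's levels. At rho 0.5, with the variances used above, iAUC variance is 0.612 against 1.612 for the unsubtracted post-meal mean; a simulation gave 85% against 46% power.
- **That about 14 points of power are lost.** The step from 80% to 94% is one favourable case, and it compares two paired analyses, neither of which is planned.

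**Conclusion.** The point holds as a minor efficiency improvement. The direction is certain: the unadjusted iAUC contrast is never more precise than the adjusted one, apart from one or two degrees of freedom. The size is not. For a marker with modest within-day correlation and similar fasting and post-meal spread, the gain could be material. For a stable marker (rho about 0.9 with equal variances), or one where k × rho is close to 1, it is negligible. All power figures rest on assumed correlations and variances and on an 80% anchor that the protocol does not claim for any marker. The loss is of precision only, and it does not undermine the secondary objective as a whole.

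**What to change.** In Section 8:
- Replace the one-way ANOVA of iAUC with a mixed model containing participant (as a random effect) and meal, with the test day's -1.5 h value as a covariate. Enter it as two terms: the man's mean baseline over his six days, and that day's deviation from it.
- State that the response is net iAUC or total AUC. With both baseline terms in the model the meal estimate is the same for these two, since total AUC is net iAUC plus a multiple of the baseline. It is not the same for a positive-only iAUC, and the present text does not say which is meant.
- Reconcile the between-meal test with the statement in Section 3.1 that control data will not be compared directly with the high-fat shake.

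The cost is a rewritten sentence or two, a slightly more complex model, and one or two residual degrees of freedom out of 20 × 6 = 120 test days. No new samples, visits or participants are needed.

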**4.4 Sample size calculation**

Based on the methodological paper by de Roos *et al. (2003) 11*we can estimate that we need 7 subjects to obtain a 6 FMD% difference before and after the fat load with 90% power and alpha of 5%, using an within-subjects SD of 2.8 FMD%. Van Oostrom *et al.*(2003) observed a reduction from 13 FMD% to 3 FMD% after a high-fat load in healthy men 4. However, we know that the within-subject coefficient of variation for FMD can be large and that FMD measures differ between studies. 13 The latter may be due to methodological reasons18. Hence we propose to include 20 subjects, which enables us to detect a difference in 3 units of endothelial function as measured with ionthophoresis (paired t-test, SD 4.5 units, power 80%, alpha 5%), which seems plausible 13.

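### The between-meal iAUC comparison uses one-way ANOVA, an independent-groups test, on repeated cross-over data, so its error term is wrong

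*Protocol*

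**What the plan says.** Section 3.1 of the protocol sets the design: "This study is a double-blind cross-over intervention (challenge) study". On replication it says "Both interventions will be performed in triplicates", and then "This means that each individual will visit the department on 6 different days". The two permitted orders are fixed: "Randomization is performed in which only the variants ABABAB and BABABA are possible". Section 4.4 gives the number of men: "Hence we propose to include 20 subjects".

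Section 8 gives two steps for secondary outcomes. First: "Changes in secondary outcome variables will be tested using repeated measures ANOVA (mixed model) using pre-defined contrasts". Then "incremental areas under the curve will be calculated for all significant altered secondary outcome variables", and these areas are "compared between meals using one-way ANOVA".

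Section 3.1 also says that the control-meal data serve to describe normal circadian rhythm in endothelial function and are not meant for direct comparison with the high-fat milkshake.

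**The concern.** Every man takes both meals, three times each, so a marker yields 20 × 6 = 120 iAUCs in 20 clusters of six. One-way ANOVA has no participant term and no participant-by-meal term. Two errors follow, and they pull in opposite directions:

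- Stable differences between men cancel when each man is compared with himself, but the test leaves them in the error. This makes it too cautious.
- If men differ in how they respond to a given meal, a man's three days on that meal are not three independent pieces of evidence. The test counts them as if they were, which makes it too liberal.

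At stake is whether the p-values of this comparison mean what they say, and whether the efficiency bought by six study days per man is used.

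**Working it through.** **The plan's nearest figure.** The protocol attaches no number to the iAUC comparison. Its sample size in Section 4.4 rests on a paired t-test (difference 3 units, SD 4.5, 80% power, 5% alpha). Reading 4.5 as the SD of the paired differences and alpha as two-sided, the exact calculation gives n = 20 with power 80.7%, so that figure reproduces. The sample-size reasoning is within-man; the iAUC test is not.

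**Inputs.** From the documents: 20 men, 2 meals, 3 days per meal. Assumed, because the protocol gives no iAUC variances: components S (between men), M (man-by-meal) and E (day-to-day), scaled so that S + M + E = 1.

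**Variance of the meal difference.**

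- True: 2M/20 + 2E/60. S cancels, and M is averaged over 20 men only.
- Assumed by one-way ANOVA on 120 values: about 2(S + M + E)/60.
- Ratio, true to assumed: (3M + E)/(S + M + E). It equals 1 when 3M + E = S + M + E, that is, when S = 2M.

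Two examples:

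- S = 0.5, M = 0, E = 0.5: true = 0 + 1/60 = 0.0167; assumed = 2/60 = 0.0333; ratio 0.50.
- S = 0.1, M = 0.4, E = 0.5: true = 0.8/20 + 1/60 = 0.0567; assumed = 0.0333; ratio 1.70.

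**If triplicates are averaged first (40 values).** True variance is 2(M + E/3)/20 and assumed variance is 2(S + M + E/3)/20. The ratio is below 1 whenever S > 0, so this version can only be conservative.

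**Simulation.** 20,000 trials per setting, nominal two-sided 5%. Power is taken at the effect for which the paired test on each man's means has 80%.

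| S | M | E | Ratio (120 values) | Type I error, one-way, 120 values | Power, one-way, 120 values | Type I error, one-way, 40 means | Power, one-way, 40 means |
|---|---|---|---|---|---|---|---|
| 0.7 | 0 | 0.3 | 0.30 | 0.1% | 29% | below 0.01% | 2% |
| 0.5 | 0 | 0.5 | 0.50 | 0.7% | 57% | 0.01% | 18% |
| 0.3 | 0 | 0.7 | 0.70 | 2.2% | 72.5% | 0.5% | 47% |
| 0.2 | 0.1 | 0.7 | 1.00 | 5.1% | 84% | 1.5% | 65% |
| 0.4 | 0.2 | 0.4 | 1.00 | 5.4% | 84% | 0.6% | 49% |
| 0.1 | 0.2 | 0.7 | 1.30 | 8.4% | not comparable | 3.0% | 76% |
| 0.1 | 0.4 | 0.5 | 1.70 | 13.8% | not comparable | 3.5% | 77% |

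Power is not comparable where the type I error is inflated. The paired test on each man's mean per meal has type I error between 4.6% and 5.2% in all seven settings.

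**The case against.** **Loose wording.** One-way ANOVA may have been meant as a one-way repeated-measures ANOVA. The preceding sentence of Section 8 names repeated measures ANOVA (mixed model) separately, so the plain reading is an independent-groups test. If a within-man test was intended, the sentence still needs changing.

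**No fixed direction.** A reader might infer that the type I error can never be 5%. The documents do not support that. At S = 2M the test is about right. The inflated rates also need M to be large relative to S and all 120 values to be entered singly. The protocol does not say whether triplicates are averaged; if they are, only power is lost. This part of the objection stands.

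**Selection.** Only markers that changed significantly reach the iAUC test, and a reader might infer that this inflates the error further. That follows if selection uses the high-fat days alone. For secondary outcomes Section 8 names no meal. If the time contrast is pooled over both meals, then in this balanced design, with equal variances under the two meals, it is independent of the meal difference and selection does no harm. Section 6.1.2 also measures some markers at the remaining times only if they have changed, so no analysis sentence could remove that selection.

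**Role of the test.** A reader might also infer that this comparison decides which markers count as specific to the high-fat meal. No section says so. Sections 1.4 and 2.1 look for biomarkers through postprandial changes correlated with the functional measurements.

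**Whether the test belongs in the plan.** Section 3.1 says that the meals are not to be compared directly. This is a fair prior question, but it does not make the named method valid while Section 8 keeps the comparison.

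**Conclusion.** The point holds. The protocol fixes a test whose error term does not fit its own design. It is not a detail left to a statistical analysis plan, because a specific method is named.

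The formula and the threshold S = 2M follow from the design, given the additive variance model with S, M and E. The size depends on variances that the protocol does not give. Over the assumed range, type I error on 120 values runs from about 0.1% to about 14%, and in the conservative settings with M = 0 power falls from 80% to 72.5%, 57% or 29%. The direction for any particular marker cannot be told from the document.

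The scope is narrow: the additional iAUC comparison of secondary outcomes. The primary outcomes and the main secondary time contrasts are assigned to a mixed model and are unaffected, as is the sample size. It should be corrected before analysis, but it does not threaten the primary conclusion.

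**What to change.** In Section 8, replace the one-way ANOVA with a linear mixed model for iAUC, with meal and visit as fixed effects and participant and participant-by-meal as random effects. A simpler alternative is a paired t-test on each man's mean of three high-fat iAUCs against his mean of three control iAUCs. It has the right error term for the meal comparison but does not adjust for visit, so the mixed model is preferable.

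Reconcile this with Section 3.1: either state there that the iAUC comparison is an intended exception, or remove the comparison from Section 8.

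The cost is a sentence in each section. No further data or participants are needed, and Section 8 already plans mixed models with the same software.

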**9. ETHICAL CONSIDERATIONS**

**9.1 Regulation statement**

The study will be conducted according to the principles of the Declaration of Helsinki (Tokyo, 2004) and in accordance with the Medical Research Involving Human Subjects Act (WMO).

**9.2 Recruitment and consent**

Recruitment will take place at the campus of Wageningen University, by means of posters and though the mailing list for potential study participants of the division of human nutrition of Wageningen University. No directly-related colleagues will be recruited for this study. An information booklet will be provided during the information meeting organized 6 weeks before the start of the study. Written informed consent will be obtained during a screening visit 4 weeks before the start of the study. In the informed consent we will ask the participants if they want to give permission for anonymous storage of their blood samples for possible additional analyses in the future. We will ask the METC for approval before performing additional analyses.

